### Sample size calculation

A total of 418 patients and 20 professionals (5 per hospital) will be required to detect an effect size of 0.3 (small) in the activity of the SLE (SLAQ) assuming a standard deviation of 8 and an intra-class correlation coefficient (ICC) of 0.01 with a power of 80% and a level of statistical significance of 5%.

### Economic evaluation

Cost-effectiveness evaluation of the multicomponent intervention will adopt the twofold of the SHS and social perspective. Effectiveness of the intervention will be measured by means of results of the SLAQ scale, along with Quality Adjusted Life Years (QALY) provided by the EQ-5D-5 L. The costs of the two comparative strategies will be calculated using the average cost estimated based on use of health resources obtained from patients during 18-month follow-up of the RCT. To allow cost-effectiveness estimation from a social perspective, information on indirect costs (travel and productivity losses) will be collected at 9 months and 18 months of follow-up. Unit costs will be taken from standard published sources when available and from specific providers. The incremental cost-effectiveness ratio (ICER) defined as the difference in average costs of each alternative (multicomponent vs. usual) divided by the difference in the average effectiveness of each alternative will be estimated. This will enable calculating the incremental cost per unit of effectiveness (SLAQ and QALY) gained from the intervention under study. Nonparametric methods will be used to calculate the confidence intervals on the ICER using the bootstrapping analysis, which will also be used to calculate the cost-effectiveness acceptability curve that shows the probability that an intervention will be cost-effective for different values of the SHS availability to pay for an additional unit of effectiveness. We will also conduct extensive deterministic and probabilistic sensitivity analyses.

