This study is not free from limitations. Firstly, the follow-up of 18 months may be insufficient to observe relevant changes in disease activity (health outcome variable), since the SLE is a disease that occurs with outbreaks. For this reason, intermediate variables (process) that measure adherence to CPG-SLE recommendations will be obtained. Secondly, both the measurement of effects and cost sharing of the intervention evaluated in this proposal will be limited to rheumatologists; professionals from other specialties involved in the care of these patients are left out of the intervention. Therefore, it is possible that both measures of effectiveness and cost-effectiveness offer conservative results (smaller effect size).

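### The bootstrap confidence interval is planned on the ICER ratio itself, which becomes hard to interpret if the resampled effect differences take both signs (minor; limited to that interval)

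*Protocol article*

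**What the plan says.** The Economic evaluation section of the protocol article defines the ICER as the difference in average costs "divided by the difference in the average effectiveness of each alternative will be estimated". It is to be reported as "incremental cost per unit of effectiveness (SLAQ and QALY) gained from the intervention under study". Its uncertainty is handled as follows: "Nonparametric methods will be used to calculate the confidence intervals on the ICER using the bootstrapping analysis". The same sentence adds a second output of that bootstrap, "which will also be used to calculate the cost-effectiveness acceptability curve that shows the probability that an intervention will be cost-effective", over different values of the health service's willingness to pay. The section then adds: "We will also conduct extensive deterministic and probabilistic sensitivity analyses".

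The section names no willingness-to-pay threshold, no bootstrap interval type and no rule by which the ICER interval would settle cost-effectiveness. It does not mention net benefit or the cost-effectiveness plane.

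Two other places bear on how near zero the effect difference may lie. The Sample size calculation section plans for an effect of 0.3 SD, which it calls small. The limitations paragraph of the Discussion says that "the follow-up of 18 months may be insufficient to observe relevant changes in disease activity" and that the effectiveness and cost-effectiveness results may be conservative.

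**The concern.** A ratio of two differences does not keep track of quadrants. Take a cost difference of size c and an effect difference of size e, both positive numbers:

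- costlier and worse: (+c)/(−e) = −c/e
- cheaper and better: (−c)/(+e) = −c/e
- costlier and better: (+c)/(+e) = +c/e
- cheaper and worse: (−c)/(−e) = +c/e

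The first two are opposite findings with the same ratio. In the last two, being below the threshold is favourable in one case and unfavourable in the other. Once replicates have effect differences of both signs, sorting their ratios and taking the 2.5th and 97.5th percentiles gives limits with no consistent meaning for the decision. A bootstrap that handles clustering and baseline adjustment perfectly would not cure this, because the fault lies in the quantity being ordered.

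At stake is one published result of the trial's cost-effectiveness aim: an interval that could look inconclusive, or favourable, when the same replicates say otherwise.

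**Working it through.** **1. The plan's own figure.** Inputs from the Sample size calculation section: effect 0.3 SD, SD 8 (so 2.4 SLAQ points), ICC 0.01, power 80%, significance 5% (taken as two-sided), 418 patients, 20 professionals.

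- Per arm without clustering: 2 × (1.960 + 0.842)² / 0.3² = 174.4, rounded up to 175, so 350 in total.
- Design effect with the professional as cluster: 1 + (418/20 − 1) × 0.01 = 1.199.
- 350 × 1.199 = 419.65, against 418 stated. The figure reproduces on this reading.

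**2. How often the SLAQ interval would include zero.** Expected effect in standard errors:

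- Without clustering: 0.3 × √(418/4) = 3.07.
- Professional as cluster: 3.07/√1.199 = 2.80. P(Z < 1.96 − 2.80) = 20%.
- Hospital as cluster (hospitals were randomised), same ICC: design effect 1 + (418/4 − 1) × 0.01 = 2.035; 3.07/√2.035 = 2.15; P(Z < 1.96 − 2.15) = 42%.
- No effect: 95%.

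No power is stated for QALYs, so the corresponding figure cannot be computed.

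**3. Share of replicates with a negative effect difference.** This depends only on the observed effect difference divided by its standard error:

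| Effect / SE | 0 | 0.5 | 1 | 1.5 | 2 | 2.8 |
|---|---|---|---|---|---|---|
| Share below zero | 50% | 30.9% | 15.9% | 6.7% | 2.3% | 0.26% |

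**4. What that does to the ratio.** The documents give no costs, QALY variances or threshold, so these are assumptions: threshold 25,000 per QALY, SE of the effect 0.02 QALY, cost difference 200 with SE 300, cost and effect independent. Net benefit is threshold × effect difference − cost difference.

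| Effect / SE | Share of ICERs below threshold | Share with net benefit > 0 |
|---|---|---|
| 0 | 79.8% | 36.5% |
| 0.5 | 79.1% | 53.4% |
| 1 | 82.2% | 69.5% |
| 2 | 93.2% | 91.5% |
| 2.8 | 98.2% | 98.0% |

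Check of the first row: mean net benefit is −200, its SE is √((25,000 × 0.02)² + 300²) = 583, and P(Z > 200/583) is about 37%.

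A dominated example: effect difference −0.04 (SE 0.02), cost difference 600 (SE 200). The percentile interval on the ICER runs from −92,857 to −664, wholly below the threshold. Mean net benefit is 25,000 × (−0.04) − 600 = −1,600, with SE √(500² + 200²) = 539, so P(net benefit > 0) is about 0.15%.

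**5. Repeated trials.** Simulation in standard-error units, threshold 1, cost and effect independent, percentile interval. The columns give the share of trials in which each interval would read as cost-effective:

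| True effect z | True cost z | ICER interval wholly below threshold | Net-benefit interval wholly above 0 |
|---|---|---|---|
| 2.15 | −2 | about 57% | about 83% |
| 1.5 | −3 | about 33% | about 89% |
| −2 (dominated) | +2 | about 50% | 0% |
| 2.8 | 0 | 47.9% | 50.6% |
| 2.8 | +1 | 23.5% | 23.8% |
| 2.15 | 0 | 28.4% | 32.4% |
| 2.15 | +1 | 12.4% | 13.2% |

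The large gaps need savings of 2 to 3 standard errors or a dominated intervention. For a cost-neutral or costlier intervention with effect z of 2.15 to 2.8, the gap is 0 to 4 points. When the true ICER equals the threshold, the error rate of the ICER interval was near nominal in the scenarios tried.

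**The case against.** The strongest reply is that the sentence does not stop at the ICER interval. It goes on to plan an acceptability curve from the same bootstrap, and that curve addresses the decision question directly. Computed from net benefit, it carries the same information as a net-benefit interval: in simulation, the share of trials with the curve above 97.5% matched the share with the net-benefit interval above zero to within 0.4 points. This stands, and it confines the point to the ICER interval. The one reservation is that the article does not say how the curve is computed. If it were built by counting ICERs below the threshold, it would inherit the fault, as the 79.8% against 36.5% above shows.

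A reader might infer that the trial's cost-effectiveness conclusion rests on this interval, so that the losses in step 5 are losses of the trial itself. The documents do not support that. They state no rule that declares cost-effectiveness when the interval lies below a threshold, and they name no threshold. In the dominated scenario, about 99% of the misleading trials also had point estimates showing a worse effect and a higher cost, which would be visible once the two differences that form the ICER are looked at.

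A reader might also infer that a naive percentile interval is fixed. The article says only that the methods are nonparametric and use the bootstrap, and a condensed article may leave the interval type to the full plan. What does stand is that the article fixes the ratio as the quantity to be given an interval.

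Finally, costs in the Health care utilization section include development, implementation and use of all components, so savings of 2 to 3 standard errors are not an obvious expectation.

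**Conclusion.** The point holds, as a minor one. Placing a bootstrap interval on the ICER is a poor choice of target when the effect difference may lie near zero, and the article's own statements make that realistic: 20% of trials at the stated power, 42% if the hospital is the cluster at the same ICC, 95% with no effect. In those circumstances a percentile interval on the ratio can be uninterpretable or point the wrong way. When the effect is clearly away from zero the matter is negligible: at 2.8 standard errors only 0.26% of replicates cross zero, and the two summaries agree (98.2% and 98.0%).

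The defect is limited to the published ICER interval, and reaches the acceptability curve only if that is built by counting ratios. The shares in steps 2 and 3 follow from the sample-size inputs and normal theory. The sizes in steps 4 and 5 are illustrations that rest on assumed costs, threshold, independence of cost and effect, and a percentile interval.

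**What to change.** In the Economic evaluation section, replace the confidence interval on the ICER with the following, all from the same bootstrap replicates:

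- 95% intervals for the cost difference, for the effect difference (SLAQ and QALY, each signed so that positive means improvement) and for the incremental net monetary benefit over a range of willingness-to-pay values;
- a statement of dominance instead of an ICER where one alternative is both cheaper and more effective;
- an acceptability curve defined as the share of replicates with positive net benefit at each willingness-to-pay value.

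This changes wording only; it needs no new data and no new resampling. The small cost is that no single interval in cost per SLAQ point or per QALY is reported.

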### Random assignment

Allocation by cluster was performed with hospitals as randomization units. After selection of professionals, an investigator blinded to hospital identity randomly assigned two hospitals to the intervention group and two hospitals to the control group by simple generation from a list of random numbers.

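### The planned ICER bootstrap makes no stated provision for hospital clustering or baseline EQ-5D, and with two hospitals per arm an ordinary bootstrap would under-cover whichever unit is resampled

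*Protocol article*

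**What the plan says.** All quotes are from the protocol article.

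- **Estimator** (Economic evaluation). The ICER is "defined as the difference in average costs of each alternative (multicomponent vs. usual) divided by the difference in the average effectiveness of each alternative". Costs of the two strategies "will be calculated using the average cost estimated based on use of health resources obtained from patients during 18-month follow-up". Effectiveness is the SLAQ result, "along with Quality Adjusted Life Years (QALY) provided by the EQ-5D-5 L".
- **Uncertainty** (Economic evaluation). "Nonparametric methods will be used to calculate the confidence intervals on the ICER using the bootstrapping analysis". The acceptability curve is to come from the same bootstrap. The unit to be resampled is not given. Deterministic and probabilistic sensitivity analyses are also planned.
- **Design** (Random assignment). "Allocation by cluster was performed with hospitals as randomization units"; the investigator "randomly assigned two hospitals to the intervention group and two hospitals to the control group".
- **Clinical endpoints** (Statistical methods). Primary and secondary endpoints get a three-level mixed model with hospital as the top level, a random intercept, and the baseline value of the outcome as a covariate. The Economic evaluation section does not refer to this model.
- **Data available.** EQ-5D-5L is collected at baseline according to both the quality-of-life section and Table 1.

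**The concern.** Cost-effectiveness stands beside effectiveness in the stated aim, and the acceptability curve is the output that a health service would act on. The section fixes three things: a contrast of averages, a nonparametric bootstrap for its interval, and the same bootstrap for the curve. A bootstrap needs enough independent units to resample. Here the independent units are hospitals, and each arm has two.

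Two things are at stake. First, if the interval under-covers, the economic result looks more certain than four hospitals can make it. Second, two hospitals against two give little protection against baseline differences. A gap in baseline utility would enter the QALY difference unless the analysis removes it, and the economic section, unlike the clinical one, does not mention doing so.

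**Working it through.** **Inputs.** From Sample size calculation: N = 418, effect size 0.3, SD 8, ICC 0.01, power 80%, alpha 5% (taken as two-sided). From Random assignment: 4 hospitals, 2 per arm. From the abstract: follow-up of 18 months (1.5 years). Assumptions, not in the document: ICC 0.01 carries over from SLAQ to costs and QALYs; 0.05 as an upper comparison; EQ-5D index SD 0.20; equal hospital sizes.

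**The plan's own figure.** The article gives no ICER interval to reproduce, but it gives a sample size.
- Per arm without clustering: 2 × (1.96 + 0.842)² × 8² / 2.4² = 174.4, so 175, or 350 in total.
- With 20 rheumatologists as clusters: m = 418/20 = 20.9; design effect = 1 + 19.9 × 0.01 = 1.199; 350 × 1.199 = 420. This reproduces the stated 418 closely.
- With the 4 randomised hospitals as clusters: m = 418/4 = 104.5; design effect = 1 + 103.5 × 0.01 = 2.035; 350 × 2.035 = 712. This does not reproduce it.

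So the sample size calculation does not itself account for hospital as the clustering unit.

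**Reading 1: patients resampled.** The true SE exceeds the bootstrap SE by the square root of the design effect.
- ICC 0.01: √2.035 = 1.43; coverage = 2Φ(1.96/1.43) − 1 = 83% (simulated 81-82%).
- ICC 0.05: design effect = 1 + 103.5 × 0.05 = 6.175; √6.175 = 2.48; coverage 57% (simulated 54-57%).

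**Reading 2: whole hospitals resampled.** Drawing two from two with replacement gives three distinct arm means, with probabilities 1/4, 1/2 and 1/4, so nine joint results. The two extreme results each have probability 1/4 × 1/4 = 1/16 = 6.25%, which exceeds 2.5%. The 95% percentile interval is therefore the full range of hospital contrasts. After removing the true effect, it misses whenever both hospitals of one arm lie above both of the other. That is 2 of the 6 equally likely orderings, so coverage is 4/6 = 67% at any ICC (simulation agrees). The acceptability curve could move only in steps of 1/16.

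**Reading 3: hospitals, then patients within them.** Simulated with normal data and 104 patients per hospital: about 90-91% at ICC 0.01 and about 78-81% at ICC 0.05.

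**Comparator.** In the same simulations a t interval on the four hospital means, with 4 − 2 = 2 df, covered about 95% at both ICCs. Its price is width: the critical value is 4.303 instead of 1.96, so against the patient-level interval the expected ratio at ICC 0.01 is about 1.43 × 4.303/1.96 = 3.1.

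**Baseline utility, if QALYs are not adjusted.**
- SE of the between-arm baseline gap at ICC 0.01: 0.20 × √(4 × 2.035/418) = 0.028.
- A one-SE gap fading linearly to zero over 1.5 years: 0.028 × 1.5/2 = 0.021 QALY.
- A one-SE gap persisting undiminished: 0.028 × 1.5 = 0.042 QALY, the upper bound for a gap of that size.
- For scale, a 0.3 SD utility effect building up linearly: 0.3 × 0.20 × 1.5/2 = 0.045 QALY.

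**The case against.** The strongest reply is that the article is silent on these points rather than wrong. A difference in averages is the generic definition of an ICER and holds equally for model-adjusted means. The bootstrap sentence fits resampling of patients, hospitals, both, or model-based quantities. EQ-5D-5L and health care utilization are listed as secondary outcomes, and Statistical methods promises multilevel, baseline-adjusted analysis of secondary endpoints; nothing bars those adjusted means from the ICER. Resampling unit and regression form are details that an article commonly leaves to a full analysis plan.

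Much of this stands. A reader might infer that the economic analysis ignores the four hospitals, that its intervals are too narrow, and that baseline imbalance passes straight into the QALY difference. The document supports none of these as fact, because it states neither the resampling unit nor that the means are unadjusted. It also stands that 0.01 is an ICC for SLAQ, that 0.05 has no source in the document, that 0.042 QALY is an upper bound, and that Statistical methods does not specify 2-df inference for the primary endpoint either.

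What does not stand is that naming the unit later would settle the matter. The article does choose a nonparametric bootstrap, and in the working above all three ordinary forms of it fall short of 95%. The two-stage form comes nearest, and at ICC 0.01 its shortfall is mild.

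**Conclusion.** The point holds as a weakness in the method chosen, not as proof of a wrong analysis. The Economic evaluation section commits to bootstrap intervals and a bootstrap acceptability curve without providing for a two-against-two hospital design, while the clinical section of the same article provides both a hospital level and baseline adjustment.

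The coverage shortfall runs from mild (two-stage resampling at ICC 0.01) to severe (patient resampling at ICC 0.05, or whole-hospital resampling at any ICC). These figures rest on equal hospital sizes, on normal data in the simulations, and on the assumed ICCs; cost data are likely to be more skewed.

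The baseline-utility part is the weaker half. It applies only if QALYs are in fact left unadjusted, and it depends on the assumed SD of 0.20. On those terms a one-SE chance gap, in either direction, would amount to roughly half to nearly all of a 0.3 SD effect (0.021 to 0.042 against 0.045 QALY).

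This should be changed before the economic analysis is run. It does not threaten the conduct of the trial.

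**What to change.** In the analysis plan, replace the bootstrap as the main economic method:

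1. Estimate incremental cost and incremental QALY by regression with hospital as the cluster level, and adjust QALYs for the baseline EQ-5D index.
2. Use small-sample inference at hospital level, on 2 df.
3. Derive the acceptability curve from net monetary benefit under that model, over a range of willingness to pay.
4. Keep any bootstrap as a labelled sensitivity analysis, with its resampling unit stated.
5. State whether the 9-month EQ-5D-5L enters the QALY area. The quality-of-life section schedules it and Table 1 does not.

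The cost is plan wording and analyst time. Baseline EQ-5D and hospital are already part of the planned data, and according to Trial status data collection was still under way when the article was submitted. The downside is wider intervals and a flatter acceptability curve, which is what four hospitals can support.

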### Duration of fieldwork

Fieldwork is estimated to last 3 years. The first year to complete recruitment of patients and rheumatologists and the following 2 years for follow-up and measurement. As interventions are maintained over time, the period of intervention and follow-up overlap (Fig. 1).

### Monitoring

Trial monitoring is the responsibility of a research team in charge of all quality control activities, assessing adherence to the trial protocol, timely work plan execution and comprehensiveness of data acquisition and data quality (databases have been designed to avoid downloading inappropriate values for every variable).

### Trial status

The trial is ongoing with patient recruitment completed June 302,019. The study is in the intervention and data collection stages at the time of the protocol manuscript submission.

## Discussion

The ongoing study is a two-arm cluster randomized controlled trial assessing the comparative effectiveness and cost-effectiveness of usual implementation of a CPG guideline to manage SLE patients against a multicomponent intervention for implementation of such CPG. The intervention combines conventional group educational and training activities promoting patient-centred care and shared decision making between patients and clinicians [25, 26], an EDS system according to SLE-CPG recommendations, and periodic feedback on their longitudinal clinical performance. Primary analysis is aimed at comparing the mean 18-month SLAQ score change from baseline among SLE patients attending hospitals assigned to the control group with the mean 18-month SLAQ score change among SLE patients attending hospitals assigned to the intervention group. Cluster randomization is used to reduce the risk of contamination bias, since the educational component of the intervention was applied to groups.

The results of this study are expected to generate scientifically valid information relevant for clinicians, managers and health policy makers; adding clinical and economic evidence to the scientific field of knowledge transfer and behaviour modification. To date, there are still few studies that assess whether implementation strategies targeting the use of CPGs are effective in patient outcomes. Even less attention has been paid to the costs of those implementation strategies despiste some authors heve revealed the importance of economic evaluation in this context [38].

Response rate of patients and difficulty obtaining all the data required are expected to be the main problems of this study. To reduce the risks of low response rates and high losses to follow-up, major effort has been made to explain to patients the objectives of the study at enrolment and during follow-up visits. Questionnaires will be completed over the phone and the option of sending these to patients by mail is always offered.

This study is not free from limitations. Firstly, the follow-up of 18 months may be insufficient to observe relevant changes in disease activity (health outcome variable), since the SLE is a disease that occurs with outbreaks. For this reason, intermediate variables (process) that measure adherence to CPG-SLE recommendations will be obtained. Secondly, both the measurement of effects and cost sharing of the intervention evaluated in this proposal will be limited to rheumatologists; professionals from other specialties involved in the care of these patients are left out of the intervention. Therefore, it is possible that both measures of effectiveness and cost-effectiveness offer conservative results (smaller effect size).

